## Abstract

**Background:**

Surgical wounds are covered to prevent bleeding, absorb the exudates, and provide a barrier against external contamination. Currently, in our hospital, after orthopedic surgery, traditional occlusive dressing of sterile gauze and non-woven hypoallergenic adhesive tape is placed. Some of the newest dressings have been shown to reduce the incidence of blisters compared with traditional dressing or colloid adhesive dressings. However, there are no comparative evaluations between the different types of dressings and their contribution to the overall results of the healing process.

**Methods/design:**

This is a randomized, controlled, open-label trial to compare five types of dressings used in total knee and hip arthroplasty surgical wounds. A total of 550 patients will be randomly allocated to one of the following dressings: (1) traditional occlusive dressing, (2) Aquacel Surgical^®^, (3) Mepilex^®^ Border Post-Op, (4) OpSite Post-Op Visible, or (5) UrgoTul^®^ Absorb Border. The dressing assigned is placed right after surgery. Patients will be followed up to 14 days after surgery when the dressing is definitively removed and will be tracked up to 3 months to record any late complications. During the immediate postoperative period and patient hospitalization and at the ambulatory visits after discharge, every time that the dressing is changed, nurses perform the study assessments. The main study outcome will be the percentage of patients with skin integrity at all times when the dressing has been changed. Skin integrity is a composite of the absence of blisters, erosion, erythema, maceration, swelling, wound dehiscence, and purulent exudates. Secondary outcomes include time to first change of dressing; percentage of patients with presence/absence of blisters, erosion, erythema, maceration, swelling, wound dehiscence, and purulent exudates; number of dressing changes needed; days of hospital stay; and nurse and patient satisfaction.

Differences in the main variable between each treatment group and group 1 will be tested by means of a chi-squared test or Fisher’s exact test. Subgroup analyses of diabetic and non-diabetic patients, patients with a body mass index of more than 30 or not more than 30, and type of surgery (hip or knee) are planned.

**Discussion:**

The results of this study will be useful for clinical decision making by giving information on the contribution of the dressings studied to the outcome of the wound and may also show which dressing offers better results depending on the characteristics of patients.

**Trial registration:**

This trial has been registered at ClinicalTrials.gov (NCT03190447). Retrospectively registered on 16 June 2017.

**Electronic supplementary material:**

The online version of this article (10.1186/s13063-018-2755-8) contains supplementary material, which is available to authorized users.

## Background

Surgical wounds are covered to prevent bleeding, absorb the exudates, and provide a barrier against external contamination. It is recognized that not covering the surgical wound in some surgeries may increase the risk of complications [1]. Leaving the wound uncovered is especially discouraged in those patients with suboptimal conditions that do not guarantee that the skin can constitute a protective barrier [2].

Surgical wound infection is the main nosocomial infection affecting postsurgical patients [3]. In our setting, the rates of superficial wound infection in 2015 were 0.51% for total knee arthroplasty (TKA) and 0% for hip arthroplasty.

Currently, in our hospital, after orthopedic surgery, traditional occlusive dressing of sterile gauze and non-woven hypoallergenic adhesive tape is placed. In some cases, we have observed the appearance of blistering, a situation that increases the risk of infection, pain, and overall costs of the procedure [4, 5]. Surgical wounds after knee and hip arthroplasty are about 15 to 19 cm long and closed with staples, and in our center no drainage is placed. After a patient is discharged from the hospital, the staples are removed when the patient is ambulatory, 10 to 15 days after the intervention. During this period, the wound is covered.

In recent years, new wound dressings have come into the market, at increased cost, and thus it is important to assess their contribution to patients before its use can become widespread [6].

Potential postoperative complications include changes in skin integrity, such as erythema, erosion, maceration, and blistering, the last of these being considered the most important. Blistering consists of the separation of dermis and epidermis, probably caused by edema and inflammation, which usually appear after the fifth or sixth day of surgery [7], leading to increased wound pain and risk of infection. These complications reduce mobilization and thus prolong the time to recover and increase hospital stay. It has been advocated that the right placement of the wound dressing is one of the most relevant factors to avoid blistering. Other predisposing factors described in the literature are obesity, venous insufficiency, diabetes mellitus, and old age [7, 8]. The incidence of blistering described for orthopedic surgery varies from 6% to 24% [7, 9].

Some of the newest pre-formed dressings have been shown to reduce the incidence of blisters in comparison with traditional dressing or colloid adhesive dressings [10]. In a recent publication, Sharma et al. [11] reviewed 12 randomized clinical studies. The authors conclude that, compared with the traditional passive dressing, new dressings could be better in terms of wound complications, although no differences in terms of surgical site infections were detected. They also emphasize that the studies comparing different new dressings are limited. This systematic review and meta-analyses also showed that there is a wide variety of products studied in studies with a small sample size and thus they are not powered to detect differences in endpoints with low frequency. Measures of satisfaction, comfort, and pain reported by patients are seldom included in the studies and neither is the nurse’s opinion or the costs. The authors suggest that well-designed studies that tackle the limitations of the existing ones are needed.

In most cases, nurses are the first ones to assess the surgical wound and decide the type of dressing placed [12]. With the objective of assessing whether newer dressings present advantages over traditional ones, a team of nurses has initiated this randomized, open-label, parallel study comparing four different types of new dressings with the traditional one used in our setting in total knee replacement and total hip replacement.

## Methods/design

### Design

This is a randomized, controlled, single-center, open-label trial to compare four types of pre-formed dressings with the traditional one used in TKA and total hip arthroplasty (THA) surgical wounds. The trial will take place in Parc Taulí Hospital Universitari in Sabadell (Barcelona, Spain). Patients undergoing TKA or THA following the fast track will be randomly allocated to receive one of the following wound dressings (description in accordance with the manufacturers’ file): (1) traditional occlusive dressing of sterile gauze and non-woven hypoallergenic adhesive tape (Fixomull^®^, BSN medical, Hamburg, Germany); (2) Aquacel Surgical^®^ (ConvaTec, Deeside, UK), which has hydrocolloid technology that allows flexing with the skin as the body moves; its hydrofiber absorbs and locks in fluid and bacteria, and its polyurethane film provides a waterproof viral and bacterial barrier; (3) Mepilex^®^ Border Post-Op (Mölnlyke, Gothenburg, Sweden), which has absorbent fibers, very high flexibility, and polyurethane backing film and is shower-proof and provides a viral and bacterial barrier; it also has wide fixation borders; (4) OpSite Post-Op Visible (Smith & Nephew, London, UK), which has hydrocellular foam, allows monitoring of progress without unnecessary dressing changes, and has waterproof film that allows showering and transpiration and provides a barrier against bacteria; or (5) UrgoTul^®^ Absorb Border (Urgo Medical, Shepshed, UK), which has a silicone adhesive border that provides non-traumatic removal and is shower-proof; its absorbent polyurethane foam allows high fluid management without maceration.

### Study population

Patients older than 18 years undergoing primary TKA and THA in the fast track and with adequate cognitive ability will be informed by the nurse during the visit performed before surgery and will be invited to participate in the study. The fast track for elective orthopedic surgery consists of a coordinated initiative with the objectives of reducing the length of hospital stay and promoting faster recovery of patients. It consists of a pre-surgical preparation of the patient, in which comorbidities and surgical risk factors (i.e. anemia and hypoalbuminemia) are assessed and corrected. Patients following this track have been carefully selected and optimized before the surgical procedure. Procedures and assessments during hospital stay and postoperative follow-up are standardized to ensure fast recovery of patients. The process also gives guidance on surgical procedures, medication before and after surgery (i.e. antibiotic prophylaxis 30 min before surgery with one dose of cefuroxime 1500 mg for THA or cefonicid 2000 mg for TKA; in case of penicillin allergy, clindamycin 900 mg), and the anesthetic technique and intra- and post-operative analgesia. Patients who have damaged skin or who are not autonomous for activities of daily living will be excluded. Patients signing the informed consent form will be included in the study.

### Random assignment

Patients will be randomly assigned to one of the five groups. A computer-generated, permuted block, random list has been created by a designated member of our institution’s Clinical Trials Unit by using WinPepi etcetera module version 3.26. Sealed envelopes for individual patients have been created for each patient. The intervention will be assigned by a nurse by opening the sealed envelope during the visit before surgery, only after the patient has signed informed consent and after his or her eligibility has been fully checked. Age, gender, body mass index (BMI), and presence of diabetes will be recorded during this visit.

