### Study procedures and assessments

On the day of surgery, the nurse in the operating room will place the dressing right after the surgery, as assigned. Information on the surgical procedure, such as length of surgery, total time of ischemia, use of a layer wound closure technique, and flexion or extension of the limb when applying the dressing (for TKA), will be recorded by operating theater nurses.

After that, patients will follow the fast track and will be discharged after 48 h in case of the absence of complications that require an extended stay. A outpatient visit is performed 7 days after the intervention. During this visit, the nurse changes the dressing and assesses the wound. On day 14 after surgery, a second nurse ambulatory visit is performed to remove the dressing, assess the wound, and remove the surgical staples. Assessment of wound during the ambulatory visits is performed by two different nurses from the study team in order to minimize the inter-observer variability. According to the current clinical practice in our hospital, during the immediate postoperative period and hospitalization, dressing is changed only in those cases when the surgeon requires it because of excessive bleeding or because of the presence of any other sign or symptom that is suggestive of wound complications. If this is the case, every time that the dressing is changed, nurses will perform the study assessments (Fig. 1. “Schedule of enrolment, interventions, and assessments”). The time spent in the procedure and the number of dressings used will also be recorded. In the event of serious health complications not related to the wound, patients will be withdrawn from the study. After the definitive removal of the dressing, patients will be tracked for the following 3 months to record any late complications, by review of the clinical records in order to detect any emergency ward visit, re-consultation, or re-hospitalization. Any untoward event detected during the follow-up (14 days) and a further 3 months will be followed up to resolution. In the event of wound complications, treatment needed (i.e. antibiotics and wound debridement) is recorded. Any other complications are recorded systematically and followed until resolution.

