#### Populations of analysis

The primary analysis will be performed according to the intention-to-treat principle and will include all randomly assigned subjects to whom the study dressing has been placed in the operation theater. Subjects will be considered and analyzed in the treatment group assigned. As no data imputation for missing values has been considered, only patients with available assessments of the main outcome will be considered in the main analysis. The final populations of analysis will be defined before the statistical analysis, and criteria will be applied to all patients regardless of the arm they have been assigned to.

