One of the main limitations of the study is the lack of blinding. The implementation of alternative procedures to guarantee the blind assessment (such as a blind evaluator) is feasible and desirable [17]; however, this was considered to be logistically too complicated and unfeasible. Although the assessments are performed by nurses and thus could be subject to subjectivity, the assessment of the presence of blister, erythema, and other endpoints will be assessed as a dichotomous variable, being less prone to bias. Assessments may also be biased by inter-observer variability. To overcome this problem, only two nurses on the team are responsible for the assessments during the scheduled ambulatory visits. However, when an unscheduled changing of dressing is carried out during hospitalization, assessments are performed by a variety of nurses, and although they are all trained in the study procedure, the inter-observer variability cannot be ruled out.

We chose, as the main endpoint, a composite variable, including any aspect of the skin that compromises skin integrity. Although this is an artificially built variable, we think it may provide good information on skin integrity. All components of the variable will also be considered as secondary variables and thus no information will be lost. Although the presence of blistering is the most frequently used primary endpoint in clinical trials comparing wound dressings, some authors have also used the concept of wound complication, including blisters, inflammation, leakage, and maceration, in a composite endpoint [13, 16].

We also included outcomes related to comfort, preferences and ease of manipulation by the nurse, time spent on the cure, and number of cures needed. These variables have not been considered in most studies and thus we consider that they add value to this investigation. Studies including these types of measures have shown the impact of the different dressings on the well-being of patients and on overall costs [4, 18, 19]. Surgical procedures may also have an impact on the outcomes measured in this trial. Factors related to surgery that influence wound healing, such as duration of surgery, total time of ischemia, and use of a layer wound closure technique, will be recorded.

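### The allocation envelope is opened at the pre-surgery visit, earlier than needed, so randomised patients can drop out of the analysis, and wounds can be closed, after the arm is known

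*Protocol article*

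**What the plan says.** Three sections of the protocol article bear on the point.

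- **Random assignment.** After consent and a full eligibility check, "The intervention will be assigned by a nurse by opening the sealed envelope during the visit before surgery".
- **Study procedures and assessments.** The dressing comes later: "On the day of surgery, the nurse in the operating room will place the dressing right after the surgery, as assigned". Theatre nurses record details of the operation, among them operating time, ischaemia time, "use of a layer wound closure technique, and flexion or extension of the limb when applying the dressing".
- **Populations of analysis.** The primary analysis is described as intention-to-treat, but it "will include all randomly assigned subjects to whom the study dressing has been placed in the operation theater". Subjects are analysed in the group assigned. Nothing is imputed, so "only patients with available assessments of the main outcome will be considered in the main analysis".

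The Design section adds: "This is a randomized, controlled, single-center, open-label trial". The Discussion grants that "Surgical procedures may also have an impact on the outcomes measured in this trial" and names operating time, ischaemia time and layered closure as factors that influence healing. Its paragraph on the lack of blinding deals with outcome assessment only. The article does not give the interval between the visit and surgery, and it does not say when the surgeon or theatre nurse learns the allocation.

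**The concern.** Two things can happen between opening the envelope and placing the dressing.

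First, a randomised patient may not reach the analysis. Surgery may be cancelled, the patient may leave the fast track or withdraw, or no study dressing may be placed. Leaving such patients out is harmless if the reason cannot depend on the arm. That is assured when nobody knows the arm until closure. It cannot be assumed when the arm has been known since the visit, and the investigators state that they expect the new dressings to do better.

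Second, staff who know which dressing will follow may, without intending it, take more or less care over haemostasis and closure. The composite outcome includes swelling, dehiscence and purulent exudate, which closure can plausibly affect.

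Both routes would bias the comparison of each new dressing with the traditional one, and a larger sample would not remove either.

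**Working it through.** **Order of events.** Consent and eligibility check, then envelope opened (Random assignment), then surgery and closure, then dressing placed (Study procedures and assessments). The analysis set is formed at the last step (Populations of analysis). Everything between the second and fourth steps takes place with the arm open, and no section states a safeguard. If the envelope were opened after closure, a cancelled patient would never be randomised, so almost nobody could be randomised and then not dressed.

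**The plan's own sample size (Sample size section).** Inputs: 82% and 95% with skin integrity, two-sided 5%, 80% power, 15% loss, 110 per group. With pooled variance and mean proportion 0.885:

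n = [1.960 × √(2 × 0.885 × 0.115) + 0.842 × √(0.82 × 0.18 + 0.95 × 0.05)]² / 0.13² = (0.884 + 0.372)² / 0.0169 ≈ 93.4, rounded up to 94.

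94 / 0.85 = 110.6, or 111 against the stated 110. The figure reproduces within rounding. In the other direction, 110 × 0.85 = 93.5 evaluable per group, with 80.1% power.

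**Loss before dressing.** The article gives no rate, so the rates below are assumptions. If this loss comes on top of the 15%, evaluable patients per group are 110 × (1 − loss before dressing) × 0.85.

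| Assumed loss before dressing | Patients of 550 | Evaluable per group | Power |
|---|---|---|---|
| 0% | 0 | 93.5 | 80.1% |
| 2% | 11 | 91.6 | 79.3% |
| 5% | 27.5 | 88.8 | 78.0% |
| 10% | 55 | 84.1 | 75.7% |
| 15% | 82.5 | 79.5 | 73.3% |

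If the 15% already covers these patients, power stays near 80%. A 2% or 5% loss before dressing then leaves 1 − 0.85/0.98 = 13.3% or 1 − 0.85/0.95 = 10.5% for later loss.

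**Why a few patients could still matter.** Under the plan's rates, the expected failures among 93.5 evaluable patients are 0.05 × 93.5 = 4.7 in a new-dressing arm and 0.18 × 93.5 = 16.8 in the control arm. An assumed 2% to 5% of 110 is 2.2 to 5.5 patients per arm, the same order as the failures in a new-dressing arm. This compares sizes only; it does not estimate bias. The effect of knowing the arm during closure cannot be quantified from the article.

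**The case against.** A reader might infer that randomised patients are in fact being lost and that theatre staff do know the dressing while they close. The article supports neither statement. It reports no such loss, and it does not say when theatre staff learn the arm. Only that they can know is supported.

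A reader might also infer that a patient given a different dressing is excluded. The phrase about the study dressing could mean any of the five, and the next sentence keeps subjects in the assigned group, so a switch between study dressings probably stays in. The wording is ambiguous rather than plainly exclusionary. The same section adds that population criteria are set before analysis and applied to all arms alike. That guards against choosing criteria by arm, but not against the events themselves depending on the arm.

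Other points for the plan carry weight. Patients are elective and optimised, with eligibility checked before the envelope is opened, and there is no evident reason why most cancellations should depend on a dressing. Wounds are stapled, no drain is placed, and the fast track gives guidance on surgical procedures, which narrows the room for closure to vary. The primary test is an unadjusted chi-squared or Fisher's exact test, so surgical factors measured after allocation do not enter it as covariates. Concealment at enrolment is not in question.

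These points limit the likely size of the problem. They do not explain why the arm needs to be known before closure, nor do they make the analysis set intention-to-treat in the usual sense.

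**Conclusion.** The point holds as an avoidable risk of bias. Allocation is revealed earlier than the design needs, no stated step withholds it from theatre, and randomised patients without a study dressing leave a set called intention-to-treat. No bias has been shown. The power cost is about 1 to 2 percentage points for an assumed 2% to 5% loss on top of the planned 15%, and close to nil if the 15% already covers it.

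Two limits apply. Late opening would not shield limb position, which is recorded as the dressing goes on and is not among the factors the Discussion names as influencing healing. Nor would it affect the unblinded outcome assessment. The change is worth making because it is cheap, not because the trial is shown to be compromised.

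**What to change.** **Timing.** Keep consent, eligibility check and baseline data at the pre-surgery visit. Send the sequentially numbered sealed envelope to theatre and have the theatre nurse open it after skin closure, for all remaining patients. Record the changeover date. With 170 of 550 included when the article was written, up to 550 − 170 = 380 allocations could be protected.

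**Population.** Restate the primary population as all randomised patients who had the surgery, analysed in the assigned arm whatever dressing was applied. Report by arm those randomised but not operated on. They cannot be analysed for the primary outcome, because without a wound it is undefined.

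**Cost.** A short amendment and a theatre briefing, with no extra staff and no change to alpha, power or sample size. The downsides are that all five dressings must be available in theatre and that the procedure changes part-way through the trial.

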### Study procedures and assessments

On the day of surgery, the nurse in the operating room will place the dressing right after the surgery, as assigned. Information on the surgical procedure, such as length of surgery, total time of ischemia, use of a layer wound closure technique, and flexion or extension of the limb when applying the dressing (for TKA), will be recorded by operating theater nurses.

After that, patients will follow the fast track and will be discharged after 48 h in case of the absence of complications that require an extended stay. A outpatient visit is performed 7 days after the intervention. During this visit, the nurse changes the dressing and assesses the wound. On day 14 after surgery, a second nurse ambulatory visit is performed to remove the dressing, assess the wound, and remove the surgical staples. Assessment of wound during the ambulatory visits is performed by two different nurses from the study team in order to minimize the inter-observer variability. According to the current clinical practice in our hospital, during the immediate postoperative period and hospitalization, dressing is changed only in those cases when the surgeon requires it because of excessive bleeding or because of the presence of any other sign or symptom that is suggestive of wound complications. If this is the case, every time that the dressing is changed, nurses will perform the study assessments (Fig. 1. “Schedule of enrolment, interventions, and assessments”). The time spent in the procedure and the number of dressings used will also be recorded. In the event of serious health complications not related to the wound, patients will be withdrawn from the study. After the definitive removal of the dressing, patients will be tracked for the following 3 months to record any late complications, by review of the clinical records in order to detect any emergency ward visit, re-consultation, or re-hospitalization. Any untoward event detected during the follow-up (14 days) and a further 3 months will be followed up to resolution. In the event of wound complications, treatment needed (i.e. antibiotics and wound debridement) is recorded. Any other complications are recorded systematically and followed until resolution.

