### Statistical methods

#### Sample size

The estimation of sample size was based on the review of previous literature [11, 14]. Our hypothesis is that 82% of patients will present skin integrity with the traditional wound dressing (group 1) during the process of wound healing and that the application of any of the other dressings studied will result in 95% of patients with skin integrity. Given a two-sided risk of 5%, a power of 80%, and an expected loss of 15%, 110 patients per group are to be included. No adjustment for multiplicity has been considered, as the comparison of the different dressings with group 1 represents distinct research questions. All tests will be performed at an alpha level of 0.05.

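### The primary analysis is labelled intention-to-treat, but the stated withdrawal and missing-data rules make it an available-case analysis, and partly observed patients are left unclassified

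*Protocol article*

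**What the plan says.** Three parts of the protocol article bear on this.

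- **Study procedures and assessments.** "In the event of serious health complications not related to the wound, patients will be withdrawn from the study". The same section says that untoward events during the 14 days and the further 3 months are followed to resolution, and that "Any other complications are recorded systematically and followed until resolution". Scheduled wound assessments are on days 7 and 14, with unscheduled ones whenever the dressing is changed in hospital.
- **Populations of analysis.** "The primary analysis will be performed according to the intention-to-treat principle", covering randomised patients whose dressing was placed in theatre, analysed in the assigned group. No imputation is planned, so "only patients with available assessments of the main outcome will be considered in the main analysis". Final populations are to be defined before the statistical analysis, with the same criteria for every arm.
- **Sample size.** Integrity of 82% on the traditional dressing against 95% on any new one, two-sided 5% risk, 80% power and "an expected loss of 15" per cent, giving 110 per group.

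The primary outcome is skin integrity at every dressing change, so it is built from more than one assessment. The trial is open-label, and the Discussion says that a blinded evaluator was considered unfeasible.

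**The concern.** A patient who leaves because of serious illness, or who does not return, may not have the same wound outcome as one who stays. If such patients drop out of the numerator and the denominator, the comparison no longer rests on the randomised groups, and an intention-to-treat label tells readers that it does.

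The composite adds a second problem. Once a component has been recorded, the patient has failed, whatever happens later. A patient who is intact on day 7 and not seen on day 14 is undetermined. If available means that all scheduled assessments are present, the known failure is discarded. If it means that any assessment is present, the undetermined patient counts as a success. The article's Background says that blisters usually appear after the fifth or sixth day, so missing later assessments matter.

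Allocation is known to everyone, so decisions on withdrawal and on the final populations can be made with knowledge of arm and, for the populations, of outcomes.

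**Working it through.** **1. The plan's own figure.** Inputs from Sample size: p1 = 0.82, p2 = 0.95, two-sided alpha 0.05, power 80%, loss 15%. The pooled normal-approximation formula is

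n = [1.96·√(2·0.885·0.115) + 0.842·√(0.82·0.18 + 0.95·0.05)]² / 0.13² = 93.3, so 94 evaluable per group.

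With loss: 94/0.85 = 110.6 (111), or 94 × 1.15 = 108.1 (109). The stated 110 reproduces. With 110 × 0.85 = 93.5 evaluable, power is 80.1%. The loss is therefore covered for power; what remains is bias and labelling.

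**2. How many patients.** 0.15 × 110 = 16.5 per group. The article does not say how much of this is withdrawal, non-attendance or loss before a dressing is placed. Steps 3 to 5 treat all of it as missing outcome after placement, which is an upper assumption.

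**3. False-positive rate under assumed one-arm differential loss.** Assume no true effect (18% failure in both arms) and 15% lost in each arm. Loss is unrelated to outcome on the traditional dressing, but a fraction f of failures is lost on the new one. Observed failure on the new dressing is 0.18 × (1 − f)/0.85, against 18% on control. Rejection rates are exact for the chi-squared test with 94 per arm.

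| f | Observed failure, new arm | False-positive rate |
|---|---|---|
| 15% (no differential loss) | 18.0% | 5.0% |
| 20% | 16.9% | 5.4% |
| 25% | 15.9% | 6.7% |
| 30% | 14.8% | 8.9% |
| 35% | 13.8% | about 12% |

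If only 5% of outcomes are missing after placement and the ratio is that of the last row (f = 5% × 35/15 = 11.7%), observed failure is 0.18 × 0.883/0.95 = 16.7% and the rate is about 5.6%.

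**4. Fragility of a positive result.** Take complete cases of 77/94 against 89/94 (81.9% and 94.7%): chi-squared p = 0.006. Add 16 lost per arm, with 3 failures among the lost controls (about their 18% rate), so control is 90/110.

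| Failures among 16 lost, new arm | New arm | Chi-squared p | Fisher p |
|---|---|---|---|
| 3 | 102/110 | 0.015 | 0.025 |
| 5 | 100/110 | 0.049 | 0.076 |
| 6 | 99/110 | 0.08 | 0.12 |

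**5. Extreme bounds.** The difference over all patients is 0.85 × 13 points + 15 points × (integrity among lost new − integrity among lost control). This runs from 11.05 − 15 = −4.0 to 11.05 + 15 = +26.1 points. A zero difference needs lost new-dressing patients to do 11.05/15, or about 74 points, worse than lost controls.

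**The case against.** Several stronger readings are tempting, and the article does not support them.

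- **That patients without a complete outcome are dropped.** The text says available, not complete. It leaves the partly observed patient open, and that gap is the problem.
- **That withdrawal plainly contradicts following complications to resolution.** A patient can leave the study and still have a complication followed for safety. The sentences need reconciling because they do not say whether wound outcomes are still collected.
- **That staff who know the dressing decide relatedness.** The sentence is passive and names nobody. The open label makes it possible; it is not stated.
- **That expected losses exceed the target effect and so could reverse the result.** The figures, 15% and 13 points, measure different things, and loss alone implies no bias. Reversal needs an extreme imbalance among the lost.

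Other points on the plan's side also stand. The article openly discloses the no-imputation rule and the lack of blinding, and it applies population criteria regardless of arm. Patients are selected and optimised before surgery, complications are expected to be few, and staple removal gives a reason to attend on day 14. Because envelopes are opened at the visit before surgery, some of the 15% may never have a dressing placed. An analysis plan that is not shown may add sensitivity analyses.

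None of this removes the core. The article itself fixes the label, the exclusion and the withdrawal, and an analysis plan cannot recover outcomes that were never collected.

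**Conclusion.** The point holds and should be fixed. On the stated rules the primary analysis is an available-case analysis, in assigned groups, of patients whose dressing was placed. Calling it intention-to-treat without qualification overstates its protection against loss related to outcome, and the treatment of partly observed patients is not fixed.

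The size of any bias cannot be known from the article, which does not predict that loss will differ by arm. Under the assumed one-arm differential loss, the false-positive rate lies between 5.4% and about 12%, and the upper end needs 35% of new-arm failures to be lost. Losing significance in a positive result takes only a moderate imbalance (6 failures against 3 among 16 lost per arm). Bringing the effect to zero takes a very large one. These are illustrations and not forecasts. The sample size is not in question.

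**What to change.** **Study procedures and assessments.** Separate stopping study participation from stopping outcome collection. Unless consent is withdrawn, day-7 and day-14 wound findings and the 3-month record review continue to be collected where possible. Reconcile this with the sentences on following complications to resolution. The change concerns data collection only, not the care of these patients.

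**Populations of analysis.**

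- Keep all randomised patients with a dressing placed in the assigned arm.
- Count any recorded component as a failure, even if later assessments are missing.
- State how a patient with no recorded failure and a missing scheduled assessment is handled.
- Call what remains an available-case analysis rather than plain intention-to-treat.
- Add a simple missing-outcome sensitivity analysis: best and worst case, or a tipping point.

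Multiple imputation may be a further sensitivity analysis but need not be primary. At 95% integrity only about 5 failures are expected among 94 evaluable patients in a new arm (0.05 × 94 = 4.7), so an imputation model fitted by arm would be fragile.

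**Cost.** A wording change, slightly more follow-up recording and a modest extra analysis; no more patients. Outcomes already lost among the 170 patients included at the time of writing may not be recoverable, so the change is worth making while recruitment continues.
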